#### Control intervention

Trial participants in the control intervention group will have access to structured online psycho-educational modules on depression (e.g. symptoms, diagnosis, treatment, medication, psychotherapy, other forms of treatment like self-help) for a duration of six weeks. There will be no therapeutic guidance or support. The participants in the control condition will be offered to inform themselves about the different aspects of depression by reading the different psycho-educational modules on their own schedule, e.g. one module per week.

### Intervention fidelity

The guiding therapists for the iFD® tool will be clinical psychologists who have qualified through completing a guidance webinar and a short test before gaining access to the tool. For the group chat, clinical psychologists will conduct the chats and will have completed a training according to the group chat intervention manual before the start of the intervention. For both interventions 1 and 2, regular supervision will be conducted by a senior psychiatrist ([name]) specializing in depression, who has been part of the project team developing the iFD® tool and has developed the manual for the clinician-guided group chat intervention.

### Outcomes and measures

#### Primary outcome

The primary outcome of the trial is depression symptomatology at the end of intervention as measured by the PHQ-A score. The depression module of the PHQ-A [32, 33] comprises nine items assessing depressive symptoms based on the diagnostic criteria for depression according to the fourth edition of the Diagnostic and Statistical Manual of Mental Disorders (DSM-IV) [48]. Respondents rate the frequency of the symptoms over the previous two weeks on a four-point Likert scale (0 = “not at all” to 3 = “nearly every day”). A sum score will be computed with higher scores indicating higher levels of depressive symptomatology. The PHQ-9 for adults has shown good reliability, validity, and sensitivity to change [49, 50].

#### Secondary outcomes

Secondary outcomes will be assessed at baseline, at the end of intervention, and at six months, one year, and two years after the start of the intervention by using the following measures: the PHQ-A [32, 33] will be used to assess depression symptomatology. Help-seeking attitudes will be assessed by the Inventory of Attitudes Toward Seeking Mental Health Services (IASMHS) [51] and actual face-to-face help-seeking will be measured with the General Help-Seeking Questionnaire (GHSQ) [52] and the Actual Help-Seeking Questionnaire (AHSQ) [53]. Adherence to the interventions (iFightDepression® and group chat) will be measured with participation rates and satisfaction with the interventions as well as possible negative effects will be assessed by the German version of the Client Satisfaction Questionnaire (ZUF-8) [54] and the Inventory for the Assessment of Negative Effects of Psychotherapy (INEP) [55], respectively. The Depression Stigma Scale (DSS) [56] will be used to assess the stigma associated with depression.

Finally, cost-effectiveness and cost-utility analyses will be conducted. Data on the cost of interventions will be compared to study outcomes to determine the incremental cost-effectiveness ratio (ICER) of interventions. The ICER is defined as the differential cost of a new treatment and treatment as usual, divided by the outcome differential of the two. Cost-utility analyses will provide information on cost per quality-adjusted life years (QALYs). QALYs are measures combining the additional life years gained by a certain healthcare intervention or program with the quality of life a subject attributes to this lifespan into one single parameter. Thus, QALYs are subjective and universally applicable outcome parameters for comparing health benefits across sectors, disorders, samples, or populations. It can be assessed in both patients and healthy individuals. Health-related quality of life will be assessed using the KIDSCREEN-10 [57, 58]. In addition, the health service utilization of the participants will be assessed by the “Mannheimer Modul Ressourcenverbrauch” (MRV) [59] and transformed into cost estimates. For this purpose, a catalog of so-called “unit costs” will be compiled for all types of treatments, services, or other healthcare measures that were used.

### Sample size calculation

We assume a small to medium effect (superiority of the two intervention groups over the control condition) on depressive symptomatology at postline after treatment as reported in meta-analyses on interventions for the prevention of depression in C&A [60]. Non-inferiority of the two active intervention groups is assumed. Repeated measures mixed models will be conducted (time*group interaction, alpha = 5%). Assuming a small to medium effect of *f* = 0.13, a lost-to-follow-up rate of 20%, and correlations of 0.2 among repeated measures, *n* = 363 individuals (*n* = 121 per group) need to be recruited for a test of the global hypothesis with 90% power. In case the ANOVA shows significant differences, post-hoc pairwise group comparisons can be conducted at a power of about 80% (Bonferroni correction) with the planned sample size.

Participants will be recruited within the ProHEAD consortium from the school-based sample of *N* = 15,000 screened C&A. Based on prevalence rates of approximately 5–12% of subthreshold depression in adolescents [14], 10% or *n* = 1500 of the screened C&A are expected to be eligible for inclusion in the trial. Thus, in order to meet the required sample size of *n* = 363, about 25% of eligible C&A would have to be willing to participate in the trial.

Criteria for the allocation of participants to the five individual ProHEAD trials are based on latest scientific evidence. However, this is the first time that the overall algorithm is applied on a consortium-wide basis simultaneously screening for various mental health problems. Therefore, an intermediate data analysis will be conducted following completion of 10% of the screening assessments (*N* = 1500) in order to determine the actual allocation ratio to the five ProHEAD trials and to adjust the screening algorithm if necessary.

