**Methods:**

The multicentre, randomized controlled E.motion trial is part of the German ProHEAD consortium (Promoting Help-seeking using E-technology for ADolescents). The objective of the trial is to investigate the efficacy and cost-effectiveness of two online interventions to reduce depressive symptomatology in high-risk children and adolescents with subsyndromal symptoms of depression in comparison to an active control group. Participants will be randomized to one of three conditions: (1) Intervention 1, a clinician-guided self-management program (iFightDepression®); (2) Intervention 2, a clinician-guided group chat intervention; and (3) Control intervention, a psycho-educational website on depressive symptoms. Interventions last six weeks. In total, *N* = 363 children and adolescents aged ≥ 12 years with Patient Health Questionnaire-9 modified for Adolescents (PHQ-A) scores in the range of 5–9 will be recruited at five study sites across Germany. Online questionnaires will be administered before onset of the intervention, at the end of the intervention, and at the six-month follow-up. Further, children and adolescents will participate in the baseline screening and the one- and two-year school-based follow-up assessments integrated in the ProHEAD consortium. The primary endpoint is depression symptomatology at the end of intervention as measured by the PHQ-A score. Secondary outcomes include depression symptomatology at all follow-ups, help-seeking attitudes, and actual face-to-face help-seeking, adherence to and satisfaction with the interventions, depression stigma, and utilization and cost of interventions.

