### Statistical analysis plan

All analyses will be conducted in accordance with intention-to-treat (ITT) principles, i.e. all randomized individuals will be included in the analysis [61]. In addition to the primary ITT analysis, per-protocol analysis will be conducted.

For the primary outcome, repeated measures mixed models (time*group interaction) will be conducted to test for differences in efficacy between the intervention groups. In case of statistically significant results, group differences will be investigated using post-hoc pairwise comparisons (Bonferroni correction). Secondary analyses using repeated measures mixed models will be performed on variables related to help-seeking behavior and depression stigma. In addition, repeated measures mixed models will be conducted to examine long-term group differences in PHQ-A scores at the six-month, one-year, and two-year follow-up timepoints, respectively. All analyses will include testing for interaction effects with study site (time*group*study site interaction).

Additionally, cost-effectiveness analyses and cost-utility analyses will be conducted. Cost-effectiveness analyses include the calculation of the ICER. The ICER indicates the additional cost for each additional (primary) outcome that has to be paid under routine care conditions. During these analyses, standard health economy techniques will be applied, such as bootstrapping techniques for estimating ICER variability, the calculation of cost-effectiveness acceptability curves (CEAC), and calculation of willingness-to-pay (WTP) criteria [62, 63]. In addition, a cost-utility study will be conducted that requires the transformation of longitudinal quality of life data (assessed with the KIDSCREEN-10) into preference measures, for the calculation of QALYs lost or gained during follow-up in order to calculate costs per QALY of the intervention.

Analyses will be performed using IBM SPSS Statistics and *p* values < 0.05 will be considered statistically significant.

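### The pairwise family is not restricted to the two comparisons with control; with all three pairs, power for each is about 73% after dropout, not about 80%

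*Protocol article*

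**What the plan says.** The abstract sets the objective as testing two interventions "in high-risk children and adolescents with subsyndromal symptoms of depression in comparison to an active control group", and the Design section frames the trial in the same way.

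The Sample size calculation section gives the expected pattern. It assumes "superiority of the two intervention groups over the control condition" and then states "Non-inferiority of the two active intervention groups is assumed". It plans a global time-by-group test at 5% and 90% power with f = 0.13, "correlations of 0.2 among repeated measures" and 20% loss to follow-up, giving 363 participants (121 per group). It adds that, if the global test is significant, Bonferroni-corrected pairwise comparisons have a power of about 80%.

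The Statistical analysis plan section says the mixed model serves "to test for differences in efficacy between the intervention groups". If it is significant, "group differences will be investigated using post-hoc pairwise comparisons (Bonferroni correction"). Neither section lists the pairs, their number or the alpha for each.

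**The concern.** Three groups have three pairs, and nothing in the text removes one. A reader would therefore divide 5% by three and test iFD against chat alongside the two comparisons with control. Yet iFD versus chat lies outside the stated objective, and the planning assumption is that the two do not differ. Spending a third of the alpha on it lowers the per-test level for the comparisons that answer the trial's question from 2.5% to 1.67%.

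At stake is whether the stated pairwise power holds for those two comparisons. There is also a smaller matter of wording: the article uses the term non-inferiority for a contrast whose only planned analysis is a test for a difference.

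**Working it through.** **Inputs from the Sample size calculation section:** f = 0.13, correlation 0.2, alpha 5%, 20% loss, N = 363 (121 per group), global power 90%, pairwise power about 80%.

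**Assumptions, not stated in the article:** two time points (baseline and end of intervention), two-sided pairwise tests, and equal effects of the two interventions, both better than control. The last is how the planning sentences read.

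**1. Reproduce the global figure.** For the within-between interaction with k = 3 groups and m = 2 times, λ = f²·N·m/(1 − ρ), df = 2 and N − 3.
- N = 303 gives λ = 0.0169 × 303 × 2/0.8 = 12.80 and power 90.0%.
- 303 × 1.2 = 363.6, which matches 363. The two-time-point model is therefore a fair reading of the plan.
- With 363 recruited and 20% lost, 290 remain and power is 88.7%, close to the stated 90%.

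**2. Turn f into a pairwise difference.** On the change score, f_change = 0.13 × √(2/0.8) = 0.2055. With two equal arms and control apart, d = f_change × 3/√2 = 0.436 SD of change. Change has variance 2(1 − 0.2) = 1.6, so this is 0.436 × √1.6 = 0.55 SD of the score.

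**3. Power for each comparison with control** (two-sided noncentral t, noncentrality d·√(n/2)). At n = 97 per arm (121 × 0.8 = 96.8) the noncentrality is 0.436 × √48.5 = 3.04. The critical values are 2.415 at 5%/3 and 2.259 at 5%/2.

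| Per arm | Three pairs (1.67% each) | Two pairs (2.5% each) |
|---|---|---|
| 97 (20% loss from 121) | 73.2% | 78.1% |
| 101 (303/3, the number behind 363) | 75.3% | 79.9% |
| 121 (no loss) | 83.6% | 87.1% |

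**4. Sensitivity.** If f = 0.13 is instead applied directly to a two-group comparison, d = 2 × 0.2055 = 0.411. At 97 per arm, power is then 67.3% with three pairs and 72.7% with two. At 121 per arm with three pairs it is 78.4%.

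**5. The conditional reading.** The article introduces the pairwise power as applying when the global test is significant. The chance that a control comparison is significant at 5%/3, given a significant global test, is at most about 0.732/0.888 = 82%, taking global power at 291 completers as 88.8%. A simulation of the same scenario (97 per arm, 200,000 runs) gives 82.6%, with 73.4% unconditionally; its pairwise tests use the variance pooled over all three arms.

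**The case against.** The strongest reply has three parts.

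First, a global test followed by all pairwise comparisons with Bonferroni correction is valid, standard and conservative. Comparing guided self-management with group chat is a reasonable question, so giving it up is a design trade-off. This stands: the plan does not inflate error, and the gain from the change is moderate.

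Second, the family of three is inferred. The stated figure of about 80% fits two comparisons better than three after dropout, which may mean that two were intended. This stands as an uncertainty. If two were intended, the power statement roughly holds, and the text needs only to name them.

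Third, about 80% can be recovered with three pairs, either by ignoring dropout (78% to 84% at 121 per arm) or by conditioning on a significant global test (about 82%). Neither is a good defence. The first drops the plan's own loss assumption. The second is not how power is normally stated, and it leaves out the trials in which the global test fails.

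A reader might also infer that the plan intends to claim non-inferiority of the two interventions and lacks the margin to do so. The article does not support this. The sentence stands among the sample-size assumptions, directly after the assumed superiority over control. No objective, outcome or analysis states a non-inferiority hypothesis. A planning assumption needs no margin, and the power of a non-inferiority test that nobody proposed measures no defect. Nor does any passage say that a null iFD-versus-chat result will be reported as non-inferiority.

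**Conclusion.** The point holds in a limited form. On the plain but unlisted reading of three pairs, a contrast outside the stated objective and assumed null takes a third of the alpha. Each comparison with control then has about 73% power at the plan's own dropout, against a stated figure of about 80%. Restricting the family to the two control comparisons gains about 5 percentage points and brings power to about 78%, close to that figure.

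These numbers rest on two time points, equal intervention effects and 97 completers per arm. Under the alternative effect translation both levels are lower, but the gain is again about 5 points. The documents do not support calling the stated 80% an outright error, because the number of pairs and the basis of the figure are not given.

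The word non-inferiority is a matter of wording only. It is still worth changing, since a non-significant difference would not show it: the 95% interval for iFD minus chat has a half-width of about 1.96 × √(3.2/97) = 0.36 SD of the score, against an assumed benefit of 0.55 SD.

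**What to change.** - In the Statistical analysis plan section, name iFD versus control and chat versus control as the confirmatory pairwise family, each tested at 2.5% after a significant global test.
- Report iFD minus chat as an estimate with its 95% CI, outside that family.
- If all three pairs are kept as confirmatory, say so, and restate the pairwise power in the Sample size calculation section as about 73% after dropout.
- Replace the non-inferiority sentence with a statement that equal effects of the two interventions are assumed for planning.

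These are text changes only, with no extra participants or data. The downside is that iFD versus chat is no longer a confirmatory test, so a difference between the two interventions could be described but not claimed under the controlled error rate.

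### The allowance for 20% loss is applied as ×1.2 rather than ÷0.8, so 363 recruited gives about 89% global power, not 90%; the pairwise power of about 80% lacks its basis and needs restating on the analysable number.

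*Protocol article*

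**What the plan says.** All the figures are in the protocol article under Sample size calculation. The test is the time-by-group interaction in a repeated measures mixed model at alpha 5%. The inputs are "Assuming a small to medium effect of *f* = 0.13", with "a lost-to-follow-up rate of 20%, and correlations of 0.2 among repeated measures". The result is that 363 individuals, 121 per group, "need to be recruited for a test of the global hypothesis with 90% power". The assumed pattern is that both interventions are superior to control, with non-inferiority assumed between the two active groups.

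The section then says that, if the global test is significant, "post-hoc pairwise group comparisons can be conducted at a power of about 80% (Bonferroni correction) with the planned sample size". It does not say how many comparisons the correction covers, what effect the pairwise contrast carries, or whether the figure is before or after loss. The Statistical analysis plan section repeats the sequence of global test and Bonferroni-corrected pairwise comparisons, also without a number of comparisons.

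**The concern.** To keep a required number after a proportion of participants is lost, that number is divided by one minus the proportion. Multiplying by one plus the proportion falls short, because the loss acts on the larger recruited number. The stated 363 looks like the product of the second operation.

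The pairwise figure matters more for interpretation, because the comparisons with control show whether each intervention works. If that figure rests on a different number of participants from the global figure, or on an unstated family of comparisons, a reader cannot tell what chance the trial has of showing an effect for either intervention.

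**Working it through.** **Inputs.** From Sample size calculation: f = 0.13, correlation ρ = 0.2, alpha = 0.05, loss 20%, power 90%, recruited N = 363. From Design and Randomization: k = 3 arms, 1:1:1. Assumption: m = 2 time points (baseline and end of intervention), inferred from the primary outcome and not stated in the sample size text.

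**Step 1: reproduce the plan's figure.** For the within-between interaction, the noncentrality is λ = f²·N·m/(1−ρ), with df1 = (k−1)(m−1) and df2 = (N−k)(m−1). Here λ = 0.0169 × N × 2/0.8 = 0.04225·N, with df1 = 2 and df2 = N−3.

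- N = 302: λ = 12.76, power 89.9%.
- N = 303 (101 per arm): λ = 12.80, power 90.0%.

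So 303 analysed participants are needed. 303 × 1.2 = 363.6, and per arm 101 × 1.2 = 121.2, which match 363 and 121. By contrast, 303/0.8 = 378.75, so 379; per arm 101/0.8 = 126.25, so 127 and 381 in total. With three, four or five time points the requirement is 246, 209 or 183. Inflated either way, these give 296 or 308, 251 or 262, and 220 or 229, so none leads to 363.

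**Step 2: global power that 363 delivers.** 363 × 0.8 = 290.4, about 97 per arm. At N = 290, λ = 0.04225 × 290 = 12.25 and power is 88.7%. The shortfall is 379 − 363 = 16 participants (18 with equal arms) and about 1.3 points of power.

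**Step 3: pairwise power.** There are two ways to set the contrast.

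(a) Apply f = 0.13 directly to two arms: λ = 0.04225 × (participants in both arms), df1 = 1.

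(b) Use the plan's pattern, both interventions equal and better than control. Three-quarters of the global λ then falls on each intervention-control contrast, so the noncentrality of the t test is √(0.75·λ), with pooled degrees of freedom. At 97 per arm, λ = 0.04225 × 291 = 12.29 and the noncentrality is √9.22 = 3.04.

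| Per arm | Comparisons | (a) f = 0.13 on the pair | (b) plan's pattern |
|---|---|---|---|
| 121 (no loss) | 3 | 78.4% | 83.7% |
| 121 (no loss) | 2 | 82.6% | 87.3% |
| 101 | 3 | 69.4% | 75.5% |
| 101 | 2 | 74.6% | 80.1% |
| 97 (after 20% loss) | 3 | 67.3% | 73.5% |
| 97 (after 20% loss) | 2 | 72.7% | 78.3% |

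More than one row is compatible with the stated pairwise figure: 121 per arm with three comparisons under (a), at 78.4%, and 101 per arm with two comparisons under (b), at 80.1%. The first ignores loss; the second allows for it, through the ×1.2 step.

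**The case against.** **A tempting stronger reading.** A reader might infer that loss was left out of the pairwise figure altogether and that the true pairwise power is 67 to 73%. The document does not support either. The row at 101 per arm with two comparisons comes closer to 80% than the no-loss row does. The stated hypothesis, each intervention superior to control, makes two comparisons a reasonable family. Three pairs is the more natural reading of unrestricted pairwise group comparisons, but it is not stated. The 67% end also carries the three-group f unchanged to a two-group contrast, which is not what the plan's pattern implies.

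**Conditional power.** The pairwise sentence applies only after a significant global test. Given that result, simulation under the plan's pattern with 97 per arm and three comparisons gives about 83%. This is a fair reading of the words. It is not the trial's chance of showing an effect, however: the probability that the global test and a given intervention-control comparison are both significant is about 73%.

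**Intention-to-treat with a mixed model.** This is the strongest objection to the 89%. Randomization follows the baseline assessment, so participants lost later still have a baseline score, and the mixed model keeps them. With unit variances, ρ = 0.2 and loss at random, the variance of an arm's mean change is (1−0.04)/97 + (1−0.2)²/121 = 0.01519, against 1.6/97 = 0.01649 with completers only. That equals about 1.6/0.01519 = 105 complete cases per arm. Put into the formulas above, this gives roughly 91% global power and, under the plan's pattern, about 77% (three comparisons) or 82% (two). The gain may well be real, but the sample size text does not claim it: its inflation for loss treats lost participants as contributing nothing. It shows that the error costs little; it does not make 363 the correct result of the stated calculation.

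**Conclusion.** The point holds as a minor arithmetic error with a related gap in the stated basis. On the plan's inputs and two time points, 363 comes from ×1.2; the number that matches 90% after 20% loss is 379, or 381 for equal arms. With 363 recruited, about 290 are analysable and global power is about 89%.

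The pairwise figure cannot be verified as written. On the analysable number, and under the plan's pattern, unconditional power for an intervention-control comparison is about 73% with three pairs (67% if f = 0.13 is put directly on the pair) and about 78% with two comparisons. Under the last reading, about 80% is close to right. No single figure applies to every pair, because the two interventions are assumed equal and their comparison has no difference to detect.

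**What to change.** Restate the global figure as: 363 randomised, about 290 analysable after 20% loss, global power about 89%. Alternatively, note that 379 to 381 is the recruitment figure that matches 90%.

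Restate the pairwise power on the same analysable number, about 97 per arm. Give the number of comparisons covered by the Bonferroni correction and the assumed contrast, and say that the figure refers to intervention against control. If it is meant as conditional on a significant global test, or if it credits baseline-only participants through the mixed model, say so.

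Restating changes text only and needs no added participants. Choosing 381 instead adds 18; the uptake needed among the 1,500 expected eligible rises from 363/1,500 = 24.2% to 381/1,500 = 25.4%, still about the 25% that the plan foresees.
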